### Participants and procedures

Participants were recruited via local newspaper articles and the website of the Chemnitz University of Technology. In addition, we received 1500 names and addresses of men and women aged ≥ 80 years from the registration office of the city of Chemnitz to enable initial contact for potential study participation. A study hotline was set up for anyone interested in study participation to call. Trained project staff determine eligibility for study participation in telephone interviews following the inclusion and exclusion criteria outlined below. People who fulfill the inclusion criteria are invited to participate in the study by mail.

#### Inclusion and exclusion criteria

Men and women aged ≥ 80 years and with their principal residence in the city of Chemnitz and surrounding areas are included in the study. Participants must be able to visit the lab independently or with the help of an accompanying person. They must be able to walk by themselves, but the use of a walking aid is allowed. Further criteria for inclusion in the study are basic knowledge of German and passing hearing and vision screening tests. Participants are excluded from the study if they present any of the criteria listed in Table 1.

**Table 1 Tab1:** Exclusion criteria of the study

**Exclusion criteria**	
- Medically prohibited to be physically active - Diagnosed psychological disorders, such as major depression, or neurocognitive disorders, such as dementia (MoCA-score < 19) - Permanent impairments due to a stroke or brain surgery - Other neurological diseases, such as epilepsy, Parkinson, or neuropathy - Severe diseases of the cardiovascular system (e.g., cardiac arrhythmia, arterial occlusive disease, heart failure) - Severe diseases of the respiratory system (e.g., COPD stage 4, severe asthma) - Severe diseases of the musculoskeletal system (e.g., arthritis, orthopedic operations in the last 6 months) - Diabetes with diagnosed neuropathy - Substance abuse - Difficulties understanding language or speech - Participant of other clinical studies, e.g., for clinical testing of new anti-dementia drugs	

#### Study design

The SENDA study is designed as a prospective cohort sequential study. After successful screening for study eligibility, participants are assigned to one of three study groups depending on their cognitive status based on their MoCA (Montreal Cognitive Assessment), CERAD-Plus (Consortium to Establish a Registry for Alzheimer’s Disease), and the FLei (‘Fragebogen zur geistigen Leistungsfähigkeit’, questionnaire for complaints of subjective cognitive disturbances) scores: 1. cognitively healthy individuals (CHI), 2. subjectively cognitively impaired persons (SCI), 3. possible mildly cognitively impaired persons due to inconclusive test results (pMCI), or mildly cognitively impaired persons (MCI). During the study period participants of four cohorts will be recruited at different time points (see Table 2). All participants complete the same cognitive, motor, sensory, and neurophysiological tests. Depending on the time point of study entry, all tests are repeated up to four times (time points: T1, T2, T3, T4) in intervals of 8 months within 3 years to identify associations with cognitive changes over time (see Fig. 1 for the study design and Table 2). The interval of 8 months was chosen according to Chamberlain et al. [55]. Only this frequency of follow-ups enables the measurements to be repeated up to three times in the defined funding period of 3 years. One test consists of three examination days of 1 to 2 h each.

**Table 2 Tab2:** Time points of study recruitment of the four cohorts and number of follow-up surveys (T1: Baseline; T2-T4: Follow-up surveys; ‘X’: participation; ‘-’: no participation)

Cohorts	T1	T2	T3	T4
Cohort 1 (begin: February 2018)	X	X	X	X
Cohort 2 (begin: July 2018)	X	X	X	-
Cohort 3 (begin: January 2019)	X	X	-	-
Cohort 4 (begin: January 2020)	X	-	-	-

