#### Cognitive status

All prior introduced neuropsychological assessments are used to establish the cognitive status of each participant at baseline and each follow-up. All criteria including cut-offs can be found in Table 3. Cognitive decline is defined as a change from CHI to SCI, pMCI, or MCI, as well as a change from SCI to pMCI or MCI or from pMCI and MCI to dementia. Individuals are categorized as having dementia when they receive a clinical dementia diagnosis outside of the study at any follow-up. Furthermore, participants are categorized as having dementia if they score less than 19 points in the MoCA [62] and perform worse than 1.5 SD below the norm in multiple cognitive domains of the CERAD-Plus. If so participants are advised to visit their general practitioner for further evaluation regarding dementia and to give a feedback to the study coordinator of SENDA as soon as possible. Additionally, functional limitations in ADL and the presence of depression will also be taken into account (see section ‘Questionnaire battery’).

**Table 3 Tab3:** Criteria for cognitive status of the participants

Group	Cognitive Status	Measures		
		MoCA	CERAD-Plus	Flei
Group 1	CHI	30–26	All tests within normal range (≤ 1.5 SD)	≤ 30
Group 2	SCI	30–26	All tests within normal range (≤ 1.5 SD)	> 30
Group 3	pMCI	30–26	1 or more tests below normal range (≥ 1.5 SD)	not considered
		< 26	All tests within normal range (≤ 1.5 SD)	not considered
	MCI	< 26	1 or more tests below normal range (≥ 1.5 SD)	not considered

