### Sample size

The sample size calculation was based on the outcome cognitive decline. Based on literature [47, 51] small to moderate effect sizes are expected. Statistical power analysis using G*Power (Version 3.1.9.4, Franz Faul, University of Kiel, Germany) showed that 200 participants are required for analysis with α = .05 and power = .80. Expecting a 20% dropout rate during the study period, 240 participants will be included.

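### Cohort 4 has no planned follow-up, yet the sample size for cognitive decline makes no allowance for it, and the dropout inflation is also too small

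*Protocol article*

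**What the plan says.** Three parts of the protocol article bear on this.

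- **Sample size.** "The sample size calculation was based on the outcome cognitive decline". The power analysis "showed that 200 participants are required for analysis with α = .05 and power = .80". The effect is described only in words: "small to moderate effect sizes are expected". The single allowance for loss is: "Expecting a 20% dropout rate during the study period, 240 participants will be included".
- **Cognitive status.** "Cognitive decline is defined as a change from CHI to SCI, pMCI, or MCI", with further transitions listed after it. Status is set at baseline and at each follow-up, and a dementia diagnosis made outside the study counts when it is received at a follow-up.
- **Study design and Table 2.** "During the study period participants of four cohorts will be recruited at different time points". T1 is baseline and T2 to T4 are follow-ups. The row "Cohort 4 (begin: January 2020" is marked for T1 and blank for T2, T3 and T4. Cohorts 1, 2 and 3 have three, two and one follow-ups.

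The article gives no cohort sizes, and no section takes Cohort 4 out of the 240.

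**The concern.** A change of status needs two observations. Cohort 4 has one by design, so none of its members can have the sizing outcome observed. That loss is planned and comes on top of dropout, but the Sample size section allows for dropout alone.

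The planned analyses do not recover it. A regression on decline has no outcome value for a person seen once. The Cox model gets no follow-up time from that person. A mixed model can use the single visit for the baseline level but not for within-person change.

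At stake is the stated power. If fewer than 200 people can supply the outcome, .80 does not describe this design, and a null result for a candidate predictor would be read with more confidence than it deserves.

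**Working it through.** **Inputs from the article.** 200 required for analysis, α = .05, power .80, 20% dropout, 240 included (Sample size); no follow-up for Cohort 4 (Table 2).

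**Not in the article.** The size of Cohort 4 (n4), a numeric effect size, the test and the number of predictors. These are assumptions below.

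**1. The 200.** It cannot be reproduced without an effect size. For the overall F test in multiple regression (noncentrality f² × N; u and N − u − 1 degrees of freedom), N = 200 gives power .80 at f² = .0396 with 1 predictor and f² = .114 with 20. Both lie between the conventional small (.02) and medium (.15) values, so 200 is plausible but cannot be verified.

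**2. The 240.** 200 × 1.20 = 240 reproduces it. But 20% dropout from 240 leaves 240 × 0.80 = 192. To keep 200 one needs 200 / 0.80 = 250. This shortfall exists whatever the size of Cohort 4.

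**3. Analysable number without Cohort 4.** If all dropouts leave before a first follow-up, n = (240 − n4) × 0.80. Power is recomputed at the f² that gives .80 at N = 200, with n rounded down.

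| n4 | 240 − n4 | n after 20% loss | Power, 1 predictor | Power, 20 predictors |
|---|---|---|---|---|
| 0 | 240 | 192 | .784 | .776 |
| 24 (10%) | 216 | 172.8 | .738 | .709 |
| 40 | 200 | 160 | .706 | .662 |
| 60 (25%, equal cohorts) | 180 | 144 | .660 | .594 |

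The first row is the dropout arithmetic alone. The rows below it add the Cohort 4 loss.

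**4. The most favourable case.** With no dropout, n = 240 − n4, which is below 200 once n4 exceeds 40. With equal cohorts this ceiling is 180, with power .757 (1 predictor) to .737 (20 predictors).

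**5. Between the two.** Let d be the proportion of Cohorts 1 to 3 lost before any follow-up. Reaching 200 needs (240 − n4)(1 − d) ≥ 200. With n4 = 0 this allows d up to 1 − 200/240 = 16.7%; with n4 = 24, up to 1 − 200/216 = 7.4%; with n4 = 40, none.

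**The case against.** **The 240 may not include Cohort 4.** The article does not map the 240 to cohorts, and the design figure is not available here. That the 240 covers all four recruited cohorts is the natural reading, but it is a reading. If the 240 meant Cohorts 1 to 3 only, the Cohort 4 loss would disappear, and 192 would remain under full early dropout.

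**Dropouts are not all lost.** The 20% refers to the whole study period. Someone in Cohort 1 or 2 who leaves after T2 already has one observed change. Removing every dropout is therefore conservative, and 144 is not a firm count. This stands, and step 5 allows for it. It does not help Cohort 3, whose only follow-up is T2.

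**A baseline-only cohort is legitimate.** A cohort-sequential design accepts unequal follow-up, and Cohort 4 can serve baseline group comparisons. This also stands: the fault is in the sample-size statement, not in having the cohort.

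**The limitation is disclosed.** The Conclusion says that the funding period and staggered entry prevent long observation of decline. It does not say that one cohort is never followed, or that power is affected.

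A reader might infer more than the article supports:

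- *That the analysable number is certainly far below 200.* This depends on an unstated n4; with a small Cohort 4 and mostly late dropout, 200 could still be reached.
- *That Cohort 4 will be entered in the regression as showing no change, which would misclassify the outcome.* Nothing in the Statistical analyses section suggests this.
- *That Cohort 4 sessions should go to a further visit for Cohort 3.* This turns on session capacity and the funding end date, neither of which is given, and correcting the text does not need it.

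**Conclusion.** The point holds as a fault in the sample-size statement. The article sizes the study on an outcome that one recruited cohort cannot supply, and counts no loss for it. It also inflates for dropout by a method that leaves 192 of the 200 it requires.

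The dropout error is certain as arithmetic. The Cohort 4 loss rests on reading the 240 as the total over four cohorts. Its direction is then clear, but its size is not known. Relative to the article's own claim that 200 gives .80, and counting every dropout as lost, power is about .71 to .74 if Cohort 4 is 10% of the sample and about .59 to .66 if cohorts are equal, over 1 to 20 predictors. These figures are illustrative: the shares are assumed, the effect sizes are back-solved, and the .80 itself cannot be checked.

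**What to change.** In the Sample size section:

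1. State that only participants with at least one planned follow-up (Cohorts 1 to 3) count toward the 200, and give the cohort sizes.
2. Correct the dropout arithmetic: 200 / 0.80 = 250, not 200 × 1.20 = 240.
3. Restate the power, or the detectable effect, for the number expected to have at least one follow-up.
4. Describe Cohort 4 as contributing to cross-sectional baseline comparisons only.

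The cost is wording and a less favourable stated power. No extra participants are needed for this. Holding to 200 after full 20% loss would need 250 in Cohorts 1 to 3 alone, which exceeds the 240 planned, so restating the power is the economical course.

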**Fig. 1 Fig1:**
[figure not shown]
Study design

### Outcome measures

Participants are invited to the labs of the study center in Chemnitz to complete the baseline (T1) and follow-up measurements (T2, T3, T4) as shown in Fig. 1. At all time points, participants undergo proven and standardized assessments, including different motor, sensory, cognitive, and electroencephalogical assessments.

### Cognitive assessments

#### Montreal Cognitive Assessment/ Consortium to Establish a Registry for Alzheimer’s Disease

To identify cognitive decline, we assess global cognition using the MoCA (Montreal Cognitive Assessment [56]) and the CERAD-Plus (Consortium to Establish a Registry for Alzheimer’s Disease [57]) tools. MoCA is a short screening tool for measuring mild cognitive impairment, i.e., in memory, attention, or executive functions. Participants can reach a maximum of 30 points [58]. The cut-off between healthy and mild cognitive impairment is set at 26 in accordance with the recommendations from Nasreddine et al. [56], which means individuals with a score of 25 or lower are considered impaired.

CERAD-Plus is a reliable and valid assessment of Alzheimer’s disease and consists of different neuropsychological tests, such as the Mini-Mental State Examination, verbal fluency, Boston Naming, word list learning, recall and recognition, constructional praxis and recall, and trail making tests A and B [57]. To detect objective cognitive impairments according to CERAD-Plus, we will compare scores in each subtest (excluding MMSE) to the age, education, and gender-controlled reference norms. Following recommendations of the National Institute on Aging-Alzheimer’s Association workgroups on diagnostic guidelines for Alzheimer’s disease [9], performances worse than 1.5 SD below the norm in one or more subtests are considered objective cognitive impairments.

#### Questionnaire for subjective assessment of mental performance (FLei)

We use the FLei (‘Fragebogen zur geistigen Leistungsfähigkeit’ [59]) to assess subjective cognitive status. The questionnaire employs 30 questions about cognitive challenges in everyday life, including items about executive functions, memory, attention, and 5 control items. Participants are asked to indicate the frequency of these challenges on a scale from 0 (‘never’) to 5 (‘very often’) and a sum score is then calculated (range 0–120). Participants with a score of 31 or higher and no objective cognitive impairment are categorized as only subjectively impaired in their cognition. This cut-off was chosen because 30 points are reached when a participant chooses 1 (‘seldom’) for every item. This is in accordance with data in other studies showing that participants on average score at the lower end of the answer range (for example *M* = 36.3 for OA with objective impairment [60] and *M* = 28.2 for a general population representative sample [61]). After completing data collection, we will also use a data driven approach to determine a suitable cut-off for our sample and, if needed, adjust the assessment of subjective cognitive status.

#### Cognitive status

All prior introduced neuropsychological assessments are used to establish the cognitive status of each participant at baseline and each follow-up. All criteria including cut-offs can be found in Table 3. Cognitive decline is defined as a change from CHI to SCI, pMCI, or MCI, as well as a change from SCI to pMCI or MCI or from pMCI and MCI to dementia. Individuals are categorized as having dementia when they receive a clinical dementia diagnosis outside of the study at any follow-up. Furthermore, participants are categorized as having dementia if they score less than 19 points in the MoCA [62] and perform worse than 1.5 SD below the norm in multiple cognitive domains of the CERAD-Plus. If so participants are advised to visit their general practitioner for further evaluation regarding dementia and to give a feedback to the study coordinator of SENDA as soon as possible. Additionally, functional limitations in ADL and the presence of depression will also be taken into account (see section ‘Questionnaire battery’).

**Table 3 Tab3:** Criteria for cognitive status of the participants

Group	Cognitive Status	Measures		
		MoCA	CERAD-Plus	Flei
Group 1	CHI	30–26	All tests within normal range (≤ 1.5 SD)	≤ 30
Group 2	SCI	30–26	All tests within normal range (≤ 1.5 SD)	> 30
Group 3	pMCI	30–26	1 or more tests below normal range (≥ 1.5 SD)	not considered
		< 26	All tests within normal range (≤ 1.5 SD)	not considered
	MCI	< 26	1 or more tests below normal range (≥ 1.5 SD)	not considered

#### Digit Symbol Substitution Test

The Digit Symbol Substitution Test (DSST), as a part of the Wechsler Adult Intelligence Scale, is a neuropsychological test for response speed, sustained attention, visual spatial skills, and set shifting. The pencil paper task is timed at 90 s. Participants have to write down the correct symbol which is paired to a series of digits from 1 to 9. The correct number-symbol matches are then calculated [63].

#### Flanker task

We use a modification of the Eriksen flanker task [64] to study attentional control and response inhibition, two executive function skills known to be impaired in patients with MCI and dementia [65, 66]. Stimuli consist of a center disk surrounded by four flanker disks set against a black background. Participants are asked to ignore the flanker disks (blue, red, or green) and react only to the center disk (red or green) by pressing the button of the correct color. The task consists of three blocks of 100 trials. One trial consists of a fixation cross (300 ms), a blank screen (200 ms), stimulus presentation (200 ms), a blank screen during the response interval (terminated by button press, maximal 3000 ms), and a blank screen (randomly chosen between 500 to 800 ms). Outcomes include response times of correct trials and accuracy.

With respect to cognitive testing, standardized methods with known psychometric properties, as well as data available about practice effects were chosen. All have good to excellent test-retest-reliability (r = .92 for MoCA [56], r = .88 for DSST [67], r = .53–.91 for subtests of the CERAD-Plus [68] and ICC = .61–.74 for RT of different trial types in the Flanker task [69]). In addition, practice effects are usually smaller for longer intervals and older participants [70].

#### Single and dual-task cognitive performance

All participants perform the modified Serial Sevens Test (SST) and Verbal Fluency Test (VFT) during single-task (while seated for 15 s) and dual-task conditions (during gait), to evaluate the cost of dual-tasking for cognitive functioning. To minimize the effects of learning the order of single and dual tasks were randomized compared to Montero-Odasso et al. [23] and Muir et al. [24]. The number of correct answers is recorded.

The modified SST [71] is a test of cognitive function. During the SST, participants are asked to successively count backwards aloud by increments of 7, starting at either 283 or 213. Due to poor cognitive functioning of most participants, a simpler version of the SST is administered, in which participants have to simultaneously count backwards by increments of 3, starting at either 153 or 183 and by increments of 1, starting at either 200 or 300.

The VFT is an additional test of cognitive function and part of the MoCA [56]. The VFT is a phonemic fluency test, in which participants are asked to generate as many words as possible within a specified time, starting with a specific letter, in this study with ‘K’ or ‘M’. Names or numbers or the same word stem are not allowed. Verbal fluency has been shown to be reduced in elderly persons with mild cognitive impairments as compared to their non-impaired persons [72].

### Neurophysiological measures

#### EEG recording

We record electroencephalograms (EEGs) in all participants with an actiCHamp system (Brain Products GmbH, Gilching, Germany) using 32 electrodes positioned according to the modified 10–20 system (Fp1, Fp2, F7, F3, F4, F8, FC5, FC3, FC1, FC2, FC4, FC6, T7, C3, Cz, C4, T8, CP5, CP3, CP1, CP2, CP4, CP6, P7, P3, Pz, P4, P8, O1, Oz, O2 with reference to Fz and a forehead ground electrode). We keep electrode-skin impedance below 25 kΩ, which is suitable for active electrodes [73]. All data are acquired at 500 Hz sampling rate in continuous recording mode. EEG is recorded during (1) resting with eyes open for 4 min, (2) resting with eyes closed for 2 min, and (3) three fine motor tasks (see below), and (4) a flanker task. Measurements take place in an electrically and acoustically shielded room with lights turned off during rest and dimly lit during task conditions. We monitor participants’ level of consciousness online in real time and annotate changes and artifacts in the EEG protocol. Total recording time is about 60 min and includes individual breaks between tasks.

#### Resting state EEG

For the rest conditions, participants are instructed to sit relaxed on a chair with both hands resting comfortably on the table in front of them. They are asked to first look at a white fixation cross at the center of a black screen for 4 min and to then close their eyes for 2 min. Similar resting state protocols are often used in aging and dementia research [74–77].

### Motor performance

#### Gait analysis

Spatiotemporal gait parameters (i.e. gait velocity, step length, step width) are collected using a walkway system for optical detection (Optogait®, Microgate, Bolzona-Bozen, Italy). Each transmitting and receiving bar consists of 96 LEDs communicating on an infrared (visible) frequency with the same number of LEDs on the opposite bar. The walking distance of each walk is 12 m and includes a turning point after 6 m. Width of the track is 1 m. Participants start 1 m before the beginning of the pathway and stop 1 m past the end. All participants perform the following walking blocks in the same order after one test trial: (1) preferred walking speed (two separate walks), (2) fast walking (one walk); and (3) dual-task walking (preferred walking and cognitive task, four separate walks). Gait performance is assessed by measuring, e.g., gait velocity, step length, and step width, as well as the variability of these parameters. All measured data are recorded and saved for analysis by the Optogait software.

Additionally, we use Kinect and XPCV framework (XPCV-Cross Platform Computer Vision Framework; www.xpcv.de) to record the 3D gait data of the participants for all conditions of the different walks. Acquired data is pre-processed to generate heat maps, and annotation assignment is done. This pre-processed data is used to train our deep learning algorithm to estimate the 3D pose of the person with our 3D pose estimation model, by several different architectures of Convolutional Neural Networks (CNN). Gait parameters are defined and abnormalities are ascertained with factors such as mean stride time, mean stride length, mean stance duration, or mean swing duration.

